**Conclusions:**

This study will demonstrate that behavioral supportive measures like physical activity may be a novel means to improve cancer related chronic pain in young survivors of childhood cancer and decrease medication usage for pain along with improvement in functional and psychosocial outcomes.

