## Objectives

2

The primary objective of this single-center, pilot randomized controlled trial is to determine the acceptability and feasibility of a 16-week behavioral PA intervention coupled with standard post-cancer directed treatment care in children and adolescent survivors of childhood cancer. The secondary objectives are to compare changes in chronic pain levels, cumulative dose of pain medications, physical function, and patient-reported outcomes within-group (CCS receiving behavioral PA intervention coupled with standard post-cancer directed treatment care and CCS receiving standard post-cancer directed treatment care alone) and between the two groups.

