### Study design

3.1

This is a single-site pilot randomized controlled trial where participants will be randomized in a 1:1 ratio to the 16-week behavioral PA intervention coupled with standard post-cancer directed treatment care, or to the standard post-cancer directed treatment care.

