### Participants eligibility

3.4

A total of 20 participants will be enrolled following these inclusion and exclusion criteria.

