### Statistical analysis

3.18

Sample size calculations were not required for this single-site, pilot randomized controlled trial. The sample size of 20 is justified due to the limited availability of participants with the specific eligibility criteria being investigated.

Acceptability will be assessed and expressed as a percentage as follows: (number of patients enrolled × 100/number of patients approached).

Feasibility will be assessed by the number of participants randomized to the behavioral PA intervention coupled with standard post-cancer directed treatment care who complete more than 50% of the intervention calculated and expressed as a percentage, as follows: (number of interventions completed × 100/number of interventions planned). To note, the planned interventions are the support calls and text messages, as follows: weekly support calls (weeks 1–4), biweekly support calls (weeks 6 and 8) and texts (weeks 5 and 7), monthly support calls (weeks 12 and 16) and texts (weeks 9, 10, 11, 13, 14, 15).

The effects of the behavioral PA activity intervention coupled with standard post-cancer directed treatment care on secondary outcomes (total self-reported pain score, cumulative dose of pain medications, functional and psychosocial outcomes) will be explored using Repeated Measures Analysis of Variance (RM-ANOVA). RM-ANOVA [49] will be used to analyze both within-group and between-group differences in intervention effects. Cohen's *d* effect sizes [50] will be reported to quantify the magnitude of differences over time and to interpret the practical significance of the findings.

Drop-out and missing data will be accounted for and reported. If the reason is an adverse event during the intervention, it will be reported as well. In case of dropouts or missing data, an intention-to-treat analysis will be performed.

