### STRENGHTS and Limitations

3.22

Findings from this study will document the acceptability and feasibility of a 16-week PA intervention coupled with standard post-cancer directed treatment care in children and adolescent survivors of childhood cancer, with chronic pain. Although our target sample size is small, pilot data from this study has the strong opportunity to demonstrate that the integrating a behavioral PA intervention into standard post-cancer directed treatment care will contribute to decreasing patient-reported chronic pain, decrease the need for pain medications, and improve functional and psychosocial outcomes in CCS.

Assuming this study is successful, our results will provide a compelling rationale to further examine the integration of behavioral PA interventions to mitigate chronic pain level from both a functional and quality of life perspective. Moreover, exploratory mechanism outcomes will have the potential to be explored, such as pain sensation, body sensation, and pain tolerance in CCS with chronic pain. The central hypothesis would be that exercise training may have the effect of decreasing pain by reframing the pain sensation and improving body sensations, along with increasing pain tolerance.

The literature is scarce regarding the potential of integrating PA into standard post-cancer directed care in CCS. It is possible that barriers such as fear of movement, which would limit the potential of promoting PA behavior changes. Future research in this area is greatly needed.

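### Within-group change is counted as an intervention effect, and the planned RM-ANOVA leaves the between-arm comparison unadjusted for baseline

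*Protocol article*

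**What the plan says.** Section 3.18 of the protocol article states that the effects on self-reported pain, cumulative dose of pain medication, and functional and psychosocial outcomes "will be explored using Repeated Measures Analysis of Variance (RM-ANOVA"), and that the method "will be used to analyze both within-group and between-group differences in intervention effects". Cohen's d is to describe the size of differences over time; the section does not say whether d is taken within or between arms. It names no baseline covariate and does not say which term of the model is the between-group result.

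The Objectives (section 2) make within-group change an aim in its own right: to "compare changes in chronic pain levels, cumulative dose of pain medications, physical function, and patient-reported outcomes within-group" and also between the two groups.

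Table 1 places self-reported pain and the psychosocial (PROMIS) outcomes at baseline, week 8 and week 16, and physical function at baseline and week 16 only.

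On size: "A total of 20 participants will be enrolled following these inclusion and exclusion criteria", "participants will be randomized in a 1:1 ratio", and "Sample size calculations were not required for this single-site, pilot randomized controlled trial".

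On claims, the Abstract concludes: "This study will demonstrate that behavioral supportive measures like physical activity may be a novel means to improve cancer related chronic pain". The last paragraph of the Introduction gives demonstrating improved pain as the reason for the trial, and section 3.22 says that "pilot data from this study has the strong opportunity to demonstrate" a benefit. Section 4 (Conclusion), by contrast, says that effectiveness is only a hypothesis at this stage.

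**The concern.** There are two weaknesses.

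The first is the standing given to within-group change. Everyone enrolled has pain at entry and finished therapy less than a year before. Some improvement over 16 weeks is plausible without any intervention, and it would appear in both arms. Section 3.18 nevertheless counts within-group differences among the intervention effects. A significant change in the intervention arm beside a non-significant one in the control arm could then be taken for benefit, although no between-arm test supports it. A within-arm Cohen's d carried into the planning of the later efficacy trial would have the same fault.

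The second is how baseline is used. A repeated-measures analysis of physical function, with one follow-up, is possible only if baseline is one of the outcomes. For pain and PROMIS that is the natural reading. The between-arm comparison then either loses precision that 20 participants can ill afford or, under a less likely reading, is diluted by a visit at which the arms cannot yet differ.

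**Working it through.** The article gives no effect size, SD, alpha, correlation or recovery size, so there is no stated figure to reproduce. The inputs from the document are 10 per arm (sections 3.4 and 3.6) and the visit times (Table 1). The assumptions are SD 1, two-sided alpha 0.05, no dropout, equal correlation r between visits, and a true week-16 difference of 0.8 SD where power is shown. Simulated figures come from 20,000 trials per setting.

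**1. Group-by-time with two visits.** This test is identical to a two-sample comparison of change scores.
- Variance of a change score: 2(1 − r).
- Residual variance after baseline adjustment: 1 − r².
- Ratio: (1 − r²) / [2(1 − r)] = (1 + r)/2.
- Cost of estimating the slope at N = 20: factor 1 + 1/(N − 4) = 1 + 1/16 = 1.0625.

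| r | (1 + r)/2 | × 1.0625 | 20 ÷ ratio | Power, change score | Power, adjusted |
|---|---|---|---|---|---|
| 0.3 | 0.65 | 0.69 | 29 | 0.30 | 0.41 |
| 0.5 | 0.75 | 0.80 | 25 | 0.40 | 0.48 |
| 0.7 | 0.85 | 0.90 | 22 | 0.59 | 0.63 |
| 0.9 | 0.95 | 1.01 | 20 | 0.96 | 0.96 |

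The fourth column is the number of participants that an unadjusted change-score analysis would need to match 20 with adjustment. The simulated standard errors agree: at r = 0.5 they are about 0.45 (change score) and 0.40 (adjusted), and (0.40/0.45)² = 0.79.

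**2. Group-by-time with three visits.** This is a joint F test on 2 and 36 degrees of freedom. Its power at r = 0.3/0.5/0.7/0.9 is 0.30/0.41/0.62/0.98 if the effect is fully present from week 8, and 0.24/0.31/0.49/0.94 if it builds up evenly to week 16. The adjusted week-16 comparison has about 0.41/0.48/0.63/0.96 in both cases. For an immediate effect the difference has almost gone by r = 0.7.

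**3. Group main effect, if that were the reported term.** It averages the arm difference over all visits, with zero at baseline.
- Three visits, constant effect δ: (0 + δ + δ)/3 = 2δ/3, so 0.8 becomes 0.53.
- Three visits, gradual effect: (0 + δ/2 + δ)/3 = δ/2, so 0.8 becomes 0.40.
- Two visits: (0 + δ)/2 = δ/2, so 0.8 becomes 0.40, with power of only 0.14 to 0.18.

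**4. Within-group tests when the intervention does nothing.** Both arms recover equally, by an assumed amount.

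| Recovery (SD) | r | Intervention arm significant | Intervention significant, control not |
|---|---|---|---|
| 0.3 | 0.5 | 14% | 12% |
| 0.5 | 0.5 | 30% | 21% |
| 0.8 | 0.5 | 62% | 24% |
| 0.3 | 0.7 | 20% | 16% |
| 0.5 | 0.7 | 45% | 25% |
| 0.8 | 0.7 | 83% | 14% |

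The last column can be checked by hand. The arms are independent, so it is p(1 − p); for example 0.30 × 0.70 = 0.21. In the same null trials every between-arm test (main effect, interaction, change score, baseline-adjusted) rejected in about 5%, with an average difference of about zero.

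**The case against.** A reader might infer that the between-arm effect itself is mixed with natural recovery. It is not. Allocation is random and concealed, so recovery and regression to the mean cancel between arms in expectation, and step 4 confirms this. Regression to the mean is also limited: entry needs pain of only 1 out of 10 for 3 months, and no functional test is an entry criterion.

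A reader might also infer that the plan will report a diluted effect. The documents do not say so. The Objectives speak of comparing changes and section 3.18 of differences over time, and both point to group-by-time, which is undiluted. On that reading the choice is between two valid estimators. The loss is one of precision, and it vanishes near r = 0.9.

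The role of baseline is a forced inference only for physical function; for pain and PROMIS it is merely the natural reading. An article may also leave contrast and covariates to a fuller document. That stands as a reason not to call them missing. It does not cover the within-group reading, which both section 2 and section 3.18 state.

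Finally, a reader might infer that the trial is set up to prove efficacy. The primary objective is feasibility and acceptability, section 3.18 calls the secondary analysis exploratory, and the Abstract's sentence is itself hedged. What remains is a conflict of wording between sections. Nor does any passage say that a significant change in the intervention arm alone would be declared a benefit; that is a risk the plan leaves open.

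**Conclusion.** The concern holds in a limited form. The firmest part is that within-group change, and any Cohen's d built on it, is not evidence of an intervention effect, yet the plan gives it that standing. With no true effect, the pattern of a significant change in the intervention arm only would arise in roughly 12% to 25% of trials over the recovery sizes and correlations assumed here.

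The second part is one of efficiency. For physical function, baseline adjustment would leave about 0.69, 0.80 or 0.90 of the variance at r = 0.3, 0.5 or 0.7, and bring nothing near 0.9. The shrinkage to 2/3 or 1/2 is conditional on the group main effect being reported.

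The third part is that the wording on demonstrating benefit in the Abstract, the Introduction and section 3.22 conflicts with section 3.18 and section 4. None of this invalidates the trial or biases its randomised comparison. It deserves correction because section 4 intends these data to lead to a fully powered efficacy trial.

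**What to change.** In section 3.18, for each secondary outcome, define the effect estimate as the between-arm difference at week 16 (and at week 8 where measured), from a model with that outcome's own baseline as a covariate. Report it with a 95% CI and a between-arm effect size. Show within-group changes descriptively, without tests, and change the within-group clause of section 2 to match. In the Abstract, the Introduction and section 3.22, replace the language of demonstrating benefit with language of estimating or exploring effects, in line with sections 3.18 and 4.

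The cost is one degree of freedom per model and more modest claims. No visit, measurement or participant is added.

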### Outcome assessments

3.9

All participants (n = 20) enrolled to participate in this study will receive baseline assessments the same day they provided assent, and their parents or legal guardians provided written informed consent. Moreover, they will receive follow-up assessments on weeks 4, 8, 12 and 16, as described in Table 1.

**Table 1 tbl1:** Outcome assessments over 16 weeks.

	Baseline	Follow-up week 1	Follow-up week 2	Follow-up week 3	Follow-up week 4	Follow-up week 5	Follow-up week 6	Follow-up week 7	Follow-up week 8	Follow-up week 9	Follow-up week 10	Follow-up week 11	Follow-up week 12	Follow-up week 13	Follow-up week 14	Follow-up week 15	Follow-up week 16
**Demographic information**	**I/C**																
**Cancer and treatment information**	**I/C**																
**Chronic pain**	**I/C**								**I/C**								**I/C**
**Pain medications**	**I/C**								**I/C**								**I/C**
**Pain medications (from medical records)**	**I/C**				**I/C**				**I/C**				**I/C**				**I/C**
**Psychosocial outcomes**	**I/C**								**I/C**								**I/C**
**PA behavior**	**I/C**	**I**	**I**	**I**	**I**	**I**	**I**	**I**	**I**	**I**	**I**	**I**	**I**	**I**	**I**	**I**	**I/C**
**Physical function**	**I/C**																**I/C**
Isometric handgrip strength	**I/C**																**I/C**
Aerobic capacity	**I/C**																**I/C**
Physical functioning	**I/C**																**I/C**

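### The plan pairs RM-ANOVA with intention-to-treat as its remedy for missing data, but that remedy does not keep a participant with a missed visit in the analysis

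*Protocol article*

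**What the plan says.** All references are to the protocol article. In Statistical analysis (3.18), the secondary outcomes (pain score, cumulative pain medication, functional and psychosocial outcomes) "will be explored using Repeated Measures Analysis of Variance (RM-ANOVA"). The same method "will be used to analyze both within-group and between-group differences in intervention effects". No other model is named for them.

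On incomplete data the section has two relevant statements: "Drop-out and missing data will be accounted for and reported", and "In case of dropouts or missing data, an intention-to-treat analysis will be performed". It names no imputation, mixed model or other route by which a participant without all visits enters the RM-ANOVA. It also does not say that such participants are removed.

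Table 1 in Outcome assessments (3.9) sets the visit pattern. Pain and psychosocial outcomes are measured at baseline, week 8 and week 16. Physical function is measured at baseline and week 16 only. Medication from records is collected at baseline and weeks 4, 8, 12 and 16. There are 20 participants, 10 per arm. Enrollment and consent/assent procedures (3.5) adds that participants who withdraw are not contacted again and may ask in writing for their data to be left out.

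**The concern.** The model and the remedy do not fit each other. Classical RM-ANOVA works on a complete participant-by-visit table, and by default a participant with one empty cell is left out altogether, including the visits that were observed. Declaring the analysis intention-to-treat does not fill the cell. As written, the analysis becomes one of completers as soon as a visit is missed.

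Two things are at stake. The first is information: with 10 per arm, losing two or three participants is a large share of the trial. The second is bias: if those who leave the PA arm are those whose pain rose, the remaining PA participants look better than the arm did. Strengths and Limitations (3.22) expects the pilot to show less pain and less medication, and the Conclusion sees it as the step to a fully powered trial. A Cohen's d taken from selected completers would be carried into that trial.

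**Working it through.** **No plan figure to reproduce.** The section states "Sample size calculations were not required for this single-site, pilot randomized controlled trial", and gives no dropout rate, SD or correlation. Every rate and correlation below is therefore an assumption.

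**1. Does RM-ANOVA accept an incomplete participant?** A standard routine (within-subject factor only) was run on 20 simulated participants with 3 visits each. It ran on complete data. With one of the 60 cells deleted it refused the data as unbalanced. The participant has to be dropped or the value filled in.

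**2. How many participants would be lost?** With miss rate q per follow-up visit, independent across visits, and v follow-ups, the expected number complete is 20(1 − q)^v.

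| q | v = 2 (pain, PROMIS) | v = 1 (physical function) |
|---|---|---|
| 5% | 18.1 | 19.0 |
| 10% | 16.2 | 18.0 |
| 15% | 14.4 | 17.0 |
| 20% | 12.8 | 16.0 |
| 30% | 9.8 | 14.0 |

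At q = 10% and v = 2 the loss is 1 − 0.9² = 19%. The chance that all 20 are complete is 0.81^20 = 1.5%.

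**3. How large can the bias be?** Assume no true effect, SD 1 at each visit and equal correlation 0.5 between visits. PA-arm participants with the worst change from baseline to week 8 leave after week 8; nobody leaves the control arm. Let D8 and D16 be the changes from baseline.

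- Var(D8) = 2(1 − 0.5) = 1, and Cov(D16, D8) = 1 − 0.5 = 0.5.
- Removing the top fraction p of D8 shifts its mean among completers by −φ(z)/(1 − p), where z is the upper p point of the normal distribution. D16 shifts by half of that.

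| p | φ(z) | Shift in week-8 change | Shift in week-16 change | Simulation, week 8 / week 16 |
|---|---|---|---|---|
| 10% | 0.175 | −0.195 | −0.10 | −0.195 / −0.097 |
| 20% | 0.280 | −0.350 | −0.175 | −0.349 / −0.171 |
| 30% | 0.348 | −0.497 | −0.25 | −0.497 / −0.250 |

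The simulation used 400,000 per arm. A regression estimate valid under missing at random, using the observed visits, gave −0.001, 0.005 and −0.003 SD for the week-16 change.

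These are biases in the change from baseline. The completers' week-16 score itself is not shifted, because Cov(week-16 score, D8) = 0.5 − 0.5 = 0. Their baseline is about 0.18 SD higher, and the change contrast (the arm-by-visit term) picks that up.

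**4. Do other mechanisms give the same result?** They do not.

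- PA-arm dropout on week-8 pain *level*, 20%, correlation 0.5: Cov(D16, week-8 score) = 0.5 − 0.5 = 0, so the week-16 change is unbiased. The week-8 change shifts by 0.5 × (−0.35), about −0.18 SD.
- A second simulation assumed correlation 0.6, a true week-16 difference of −0.50 SD and about 15% to 22% dropout per arm. Completers gave −0.50 under completely random dropout, −0.495 when dropout followed baseline pain equally in both arms, and −0.42 when it followed baseline pain in the PA arm only. That last bias is against the intervention.
- In the same simulation, when dropout followed the unseen week-16 pain in the PA arm only, completers gave −0.55 and the missing-at-random method gave −0.58. The usual fix does not remove that bias.

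**The case against.** The best defence is that the article never commits to deleting incomplete participants. It says missing data will be accounted for, and RM-ANOVA after imputation would satisfy both sentences; the imputation detail could stand in a full protocol or analysis plan that is not shown. This stands in part. A reader might infer that the promised intention-to-treat analysis cannot be delivered at all, and the document does not support that. But the article is not silent: it fixes a complete-data method and offers as its remedy something that does not repair it. That mismatch is in the text itself.

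A reader might also infer that any dropout linked to pain biases the comparison. The calculations contradict this: the bias depends on whether dropout follows worsening or level, and whether it differs by arm. Nothing in the protocol shows which mechanism will occur. The 20% scenario means 2 of 10 PA participants, and with 10 against 8 the standard error of the change difference is about √(1/10 + 1/8) = 0.47 SD, nearly three times the week-16 bias of 0.17 SD. In a trial of this size noise exceeds the bias, though bias does not average out when the estimate is passed on.

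It is tempting to extend the 10% miss rate to the four medication follow-ups (1 − 0.9⁴ = 34%). That does not hold: those data come from chart review and the prescription monitoring database (3.14), so a missed visit does not by itself remove them.

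Finally, reading the last sentence of 3.18 as making intention-to-treat conditional on dropout is somewhat harsh. The article proposes no per-protocol or as-treated analysis. Stating the rule unconditionally is a matter of clear wording.

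**Conclusion.** The point holds in limited form. The analysis as stated does not deliver intention-to-treat once a visit is missed, because RM-ANOVA is named without a compatible way to handle missing values. The expected loss is about 19% of participants for pain and PROMIS outcomes, if 10% of visits are missed independently. The false benefit of 0.10 to 0.25 SD in the week-16 change and 0.20 to 0.50 SD in the week-8 change rests on three assumptions: correlation 0.5, dropout in the PA arm only, and dropout driven by worsening at week 8. It shows what can happen and does not predict what will.

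Severity is moderate. A reader might take this as a flaw that undermines the trial, but the outcomes concerned are exploratory secondary ones in a 20-person pilot, and neither the acceptability nor the feasibility percentage uses RM-ANOVA.

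**What to change.** - Replace RM-ANOVA with a likelihood-based linear mixed model containing arm, visit and arm-by-visit, with small-sample degrees of freedom (REML with Kenward-Roger, for example). Use all observed visits of all randomised participants in their assigned arm.
- State intention-to-treat as the rule for all analyses, not as a response to dropout. Report how many participants had data removed at their own request, since no model can recover those.
- Add one sensitivity analysis that gives unfavourable values to PA-arm dropouts. The mixed model assumes missing at random, and step 4 shows that it does not protect against dropout driven by unseen pain.

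The gain is mainly for outcomes with an intermediate visit (pain and PROMIS). It is small for physical function, which has only baseline and week 16. The cost is a change of wording and a little more analysis work; no new data are needed.
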